# Secondary endpoints

Secondary endpoints included the St. George's Respiratory Questionnaire (SGRQ) score, developed as a specific health-related QOL measure for respiratory diseases; Euro Qol 5 Dimension (EQ-5D) index, a QOL assessment instrument used to calculate quality-adjusted life years in the economic evaluation of medical technology; and Self-Care Capacity Questionnaire score, a measure of the degree of patient self-care. respiratory function measurements; and 6-min walk test distance will be collected at baseline and 12 and 24 weeks after enrollment. In addition, as an objective measure of physical activity, the average number of steps taken and amount of activity will be collected from an activity meter at 12 and 24 weeks after enrollment.

# Centralized evaluation system

This study does not use a centralized evaluation system.

# Registration and allocation

# Registration

1. Registration procedure

The attending physicians at the Department of Respiratory Medicine of Tohoku University Hospital and each collaborating institution will select the participants and distribute the survey instructions during regular outpatient visits. Participants who read the study description and are interested in the study will, of their own free will, inquire about an initial interview with the investigators. At the initial interview, the eligibility criteria will be confirmed and the survey will be explained orally and in writing; further, the participants will be enrolled in the study upon submission of a participant consent form.

1. Notes on registration

To avoid duplication of enrollees, a list of enrollees will be created and maintained. In addition, since it is anticipated that the required number of participants will not be gathered after the study begins, participants will be added to the list via a sequential enrollment method.

# Allocation

1. Assignment method and assignment adjustment factors

A table will be created in advance to randomly assign the expected number of participants to the intervention and control groups. Consenting participants will be assigned a serial number and anonymized in a consolidated manner. Research assistants will assign participants to the intervention and control groups by fitting the participants to a random number table generated from the serial numbers. Concerning allocation adjustment, since the study is a multicenter study, it will be necessary to allocate the participants to each facility, since different facilities are considered to have different medical systems.

# Number of planned cases and basis for setting

# Planned number of cases

The intervention and control groups are expected to have 17 patients each; hence, the total expected number of patients is 34.

# Basis for setting

The primary hypothesis of this study is: A group of patients with chronic respiratory failure receiving NPPV with a tele-nursing intervention program (intervention group) will have fewer temporary outpatient visits (percentage and number of visits) due to acute exacerbations during the intervention period than a control group receiving only usual care (Figure 1). Based on the literature [24], we assumed that the average number of visits to the emergency department due to acute exacerbations of chronic respiratory diseases would be 2.4 visits/year for NPPV users and 1.6 visits/year for NPPV non-users to reduce the number of outpatient visits by 1.0 visit/year. The significance level, power of the study, and standard deviation of the number of improvement of visits are 5%, 80%, and 1.0 visit/year, respectively. In addition, assuming a dropout rate of 10% of the total number of patients, the intervention and control groups were calculated to require 17 patients each, for a total of 34 expected enrollees in both groups.

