# Objective

The effectiveness of an ICT-based tele-nursing intervention program for patients with chronic respiratory failure undergoing NPPV in home care will be examined in terms of the number of readmissions and occasional visits due to acute exacerbations or chronic respiratory diseases, with readmission and occasional visit rates as primary endpoints.

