# Statistical analyses

# Statistical analysis methods

Data on basic participant characteristics will be examined for normality using the Kolmogorov-Smirnov test, and the differences between the means or medians for the data in the intervention and control groups will be compared using the *t*-test, based on the normality of the data. Fisher's exact test will be used to compare the primary endpoints of temporary outpatient visit and readmission rates between groups, and student *t*-test will be used to compare the number of temporary visits and readmissions between groups. Paired *t*-tests will be used to compare changes in secondary endpoints at baseline, 12 weeks after enrollment and intervention initiation, and 24 weeks after enrollment and intervention initiation (at the end of the intervention period). The analysis will be conducted using a personal computer with Microsoft Windows 8.1 OS installed and IBM SPSS version 21.0 statistical software, with a two-tailed significance level of 5%.

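### The 80% power covers only a comparison of mean visit numbers; the visit and readmission rates, also called primary and tested with Fisher's exact test, were never sized

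*Protocol*

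**What the plan says.** **Sizing.** Section 9.2 states the primary hypothesis that the intervention group "will have fewer temporary outpatient visits (percentage and number of visits) due to acute exacerbations during the intervention period". It then assumes that emergency visits "would be 2.4 visits/year for NPPV users and 1.6 visits/year for NPPV non-users", and aims "to reduce the number of outpatient visits by 1.0 visit/year". It continues: "The significance level, power of the study, and standard deviation of the number of improvement of visits are 5%, 80%, and 1.0 visit/year, respectively". Finally, "assuming a dropout rate of 10% of the total number of patients", it arrives at 17 per group, 34 in total. No proportion of patients with a visit or a readmission is given in section 9.2, in the Overview, or anywhere else.

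**Which endpoint is primary.** The protocol answers this in three ways:
- *Rates:* the Objective section ends "with readmission and occasional visit rates as primary endpoints". Section 10.1 says "Fisher's exact test will be used to compare the primary endpoints of temporary outpatient visit and readmission rates between groups".
- *Numbers:* the schema in the Overview lists the numbers of hospitalizations, hospital days and unscheduled visits. The overview of the distance nursing intervention program also calls the numbers of visits and readmissions primary.
- *Both:* the Primary endpoints section and the hypothesis in section 9.2 (also in Research design) list rate and number together.

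**Tests.** Section 10.1 uses Fisher's exact test for the rates and Student's t-test for the numbers, "with a two-tailed significance level of 5" per cent. Nothing ranks rates against numbers or says which of them the 80% covers.

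**The concern.** A reader of section 9.2 will take the 80% to cover both halves of the hypothesis it follows. A calculation from a mean difference and an SD says nothing about the power to compare two proportions. Reducing a count to at least one visit versus none also discards information, and Fisher's exact test is conservative in groups of 17.

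At stake is how a non-significant Fisher result will be read. If the stated 80% is believed, that result looks like evidence that the programme does not work. If the true power is a small fraction of that, it carries little information. For readmissions there is no planning value at all. The interim analysis in section 10.2 applies the same methods at 12 weeks, where fewer visits will have accrued.

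**Working it through.** **Inputs from the protocol.** Two-sided 5% (10.1); target power 80%, difference 1.0 visit/year, SD 1.0 visit/year, 10% dropout, 2.4 visits/year in NPPV users (9.2); 17 per group; 24-week intervention with assessments at 12 and 24 weeks.

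**Inputs assumed here.** (a) The intervention mean is 2.4 − 1.0 = 1.4 visits/year; the protocol does not print 1.4. (b) A count distribution, of the same shape in both arms, to turn means into proportions; the protocol gives none.

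**Step 1: reproduce the 17.**
- Normal approximation for two means: n = 2(1.960 + 0.842)² × (1.0/1.0)² = 15.70 per group. Dropout gives 15.70/0.9 = 17.4, or 15.70 × 1.1 = 17.3; either is 17 to the nearest whole number.
- Noncentral t: n = 16.71, so 17 per group (power 80.7%) with no dropout allowance.

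The protocol does not show which route was taken. Both are comparisons of means.

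**Step 2: convert to proportions.** With m = annual rate × weeks/52, the probability of at least one visit is:
- Poisson: 1 − exp(−m)
- Negative binomial, dispersion k: 1 − (1 + km)^(−1/k)
- Normal, using 1.0 as the SD of annual counts with variance proportional to time: probability of exceeding 0.5 visits

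Example, 24 weeks, Poisson: control m = 2.4 × 24/52 = 1.108, giving 67.0%; intervention m = 1.4 × 24/52 = 0.646, giving 47.6%.

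**Step 3: Fisher power.** All 2×2 tables at 17 per group were enumerated and the probabilities of those with two-sided p ≤ 0.05 were summed. The last column uses 15 per group (17 × 0.9 = 15.3).

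| 2.4 vs 1.4 visits/year | Proportions | Power, n = 17 | Power, n = 15 |
|---|---|---|---|
| 12 weeks, Poisson | 42.5% vs 27.6% | 8.0% | 5.9% |
| 12 weeks, neg. binomial, k = 0.5 to 2 | 38.7% vs 25.9% to 31.1% vs 22.1% | 6.3% to 4.2% | 4.9% to 3.5% |
| 12 weeks, normal | 54.5% vs 35.6% | 12.3% | 8.5% |
| 24 weeks, Poisson | 67.0% vs 47.6% | 12.9% | 9.0% |
| 24 weeks, neg. binomial, k = 0.5 to 2 | 58.6% vs 42.9% to 44.2% vs 34.0% | 9.1% to 4.8% | 6.2% to 3.4% |
| 24 weeks, normal | 81.4% vs 58.5% | 18.9% | 14.9% |
| Full year, Poisson | 90.9% vs 75.3% | 12.0% | 9.3% |

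At 17 per group the range over 12–24 weeks is about 4–19%. A full year of counting does not repair it.

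**Step 4: stress the assumptions.**
- Control rate 1.6 instead of 2.4 (1.6 vs 0.6, Poisson): 27% at 24 weeks, 43% over a year. But 1.6 is the figure for non-users of NPPV, and the trial enrols users.
- From a 67% control proportion, 80% power needs an intervention proportion of about 16%.
- An artificial bound, with every control patient having a visit and no intervention patient more than one over 24 weeks (100% vs 64.6%), gives 78%. The two arms then no longer share a count distribution, so this is not a planning scenario.

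**Step 5: the count t-test.** The effect and SD in section 9.2 are per year. Simulating Poisson counts at 2.4 vs 1.4 per year, 17 per group, the t-test has about 29% power over 24 weeks and 54% over a full year.

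**The case against.** **The numbers are primary too.** The schema and the description of the intervention program name only numbers, and sizing on one of several primary endpoints is common. This stands. A reader might infer that the whole trial has single-digit or low-teens power for its primary endpoint; the documents do not support that, because they do not make the rates the sole primary endpoint. A ranking could also sit in a statistical analysis plan that is not at hand. But the protocol itself attaches the 80% to a hypothesis that includes the percentage and calls the rates primary in two places.

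**The Fisher figures rest on assumed distributions.** This also stands. The protocol gives no proportions, 1.4 is inferred, and the SD is described as that of an improvement, so using it as the SD of raw counts is a further assumption. A narrow power figure cannot be presented as the plan's own. What survives is the distance from 80%.

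**The 17 need not come from the t-test.** Correct: the normal approximation with dropout also gives 17. The argument needs only that both are means calculations.

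**The sizing is then sound for the counts.** A reader might infer this too. It does not follow, because an annual effect and SD are applied to a 24-week trial (step 5).

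**Conclusion.** The point holds in limited form. The single 80% in section 9.2 comes from a comparison of means and cannot be claimed for the percentage half of the hypothesis or for the rates called primary in the Objective and section 10.1. Those rates are unsized, and the readmission rate has no assumed effect. That much rests on the text alone.

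The size of the shortfall is illustrative: about 4–19% at 17 per group over 12–24 weeks, given 2.4 vs 1.4 visits/year and a common count distribution in both arms. Under those assumptions Fisher's test would miss the assumed effect in roughly 81–96% of trials. The gap from 80% is large under every such distribution tried and does not depend on the follow-up window.

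The protocol's disagreement with itself about the primary endpoint is part of the fault and has to be resolved with it.

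**What to change.** 1. In section 9.2, state that the calculation covers only the mean number of temporary visits, and take the percentage out of the powered hypothesis. Align the planned-cases text in the Overview and the hypothesis in Research design.
2. Reconcile the schema, the Objective, the overview of the intervention program, Primary endpoints, 9.2 and 10.1 so that the number of temporary visits is the primary endpoint. Make the visit and readmission rates supportive, reported as risk differences with 95% confidence intervals.
3. If the rates stay primary, say that the 80% does not apply to them and give their illustrative power as a range with its assumptions. Add that a non-significant Fisher result is not evidence of no effect.
4. Do not reaffirm 80% for the t-test on visit numbers until effect and SD are restated for the 24-week window.

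**Cost.** Steps 1–3 need no extra patients or data. The rates lose primary status, or a much lower power is printed for them. Restating the count calculation may show that 34 patients are too few. Under section 27, changes affecting the primary endpoints or the evaluation of efficacy are amendments, so ethics review and institutional approval are needed.

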# Statistical analyses

# Statistical analysis methods

Data on basic participant characteristics will be examined for normality using the Kolmogorov-Smirnov test, and the differences between the means or medians for the data in the intervention and control groups will be compared using the *t*-test, based on the normality of the data. Fisher's exact test will be used to compare the primary endpoints of temporary outpatient visit and readmission rates between groups, and student *t*-test will be used to compare the number of temporary visits and readmissions between groups. Paired *t*-tests will be used to compare changes in secondary endpoints at baseline, 12 weeks after enrollment and intervention initiation, and 24 weeks after enrollment and intervention initiation (at the end of the intervention period). The analysis will be conducted using a personal computer with Microsoft Windows 8.1 OS installed and IBM SPSS version 21.0 statistical software, with a two-tailed significance level of 5%.

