# Interim analysis and early termination of studies

An interim analysis will be conducted 12 weeks after the start of the intervention and enrollment to determine if the main objective has been achieved. The same methods of analysis will be used as for the main analysis. Even if the planned number of study participants is not attained as a result of the interim analysis, the study may be terminated early, if the superiority of the intervention group is deemed sufficient. The study will also be terminated if adverse events related to the intervention occur in 10% or more of the total number of participants.

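### Fisher's exact test for the primary visit and readmission proportions is valid but conservative at about 17 per group; Boschloo's exact test would recover some power under the same 5% ceiling per test

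*Protocol*

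**What the plan says.** Protocol section 10.1 (Statistical analysis methods) states that Fisher's "exact test will be used to compare the primary endpoints of temporary outpatient visit and readmission rates between groups" and that the numbers of visits and readmissions will be compared by Student's t-test, all "with a two-tailed significance level of 5" per cent.

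Section 9.1 fixes the size: "The intervention and control groups are expected to have 17 patients each". Section 9.2 derives it from mean counts. The aim there is "to reduce the number of outpatient visits by 1.0 visit/year", and significance level, power and standard deviation are "5%, 80%, and 1.0 visit/year, respectively", "assuming a dropout rate of 10% of the total number of patients". The primary hypothesis in the same section covers proportions as well as counts: the intervention group "will have fewer temporary outpatient visits (percentage and number of visits) due to acute exacerbations during the intervention period".

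Section 10.2 adds a 12-week interim analysis that may stop the trial for superiority: "The same methods of analysis will be used as for the main analysis". The protocol gives no expected proportion of patients with a visit or readmission, and no power for the comparison of proportions.

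**The concern.** Fisher's test takes as fixed the total number of patients with an event. The design does not fix that total. With about 17 patients per group, this conditioning leaves few attainable p-values, and the largest one at or below 0.05 is often well below it. The chance of a false positive is then lower than the 5% allowed, and power is lost with it.

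The protocol commits to this test by name for a primary comparison, so the choice can be judged at the planned size. At stake is some power in a 34-patient trial, which could be recovered without enrolling anyone. For example, 8 of 17 against 2 of 17 with an event (47% v 12%) gives a Fisher p-value of 0.057. It would be declared non-significant, although an exact test that also guarantees at most 5% rejects it.

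**Working it through.** **1. The plan's own figure.** For a difference of 1.0 and SD 1.0 (section 9.2), the normal formula gives n = 2 × (1.960 + 0.842)² × 1.0² / 1.0² = 15.7, so 16 per group. The t-based value is 16.7, so 17. Dividing by 0.9 for dropout gives 18 or 19. The stated 17 therefore matches the t-based number before dropout. For this point it matters only that 17 and the 80% both come from a comparison of means.

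**2. Analysed numbers.** With 10% dropout, 34 × 0.9 = 30.6. About 30 or 31 patients would be analysed, for example 15 v 15 or 16 v 15. Other splits are possible.

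**3. True error of each test.** For groups of n₁ and n₂ and a common event rate p, the size of a rejection region R is the sum, over all tables (a, b) in R, of Bin(a; n₁, p) × Bin(b; n₂, p). The maximum is taken over a fine grid of p from 0.0005 to 0.9995.
- Fisher: R is every table with two-sided p ≤ 0.05.
- Boschloo: R is every table with a Fisher p-value up to the largest cut-off that keeps the maximum size at or below 5%. At 17 v 17 the cut-off is 0.0799.

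| Analysed | Fisher, max. size | Boschloo, max. size | Tables only Boschloo rejects |
|---|---|---|---|
| 17 v 17 | 2.44% | 4.31% | 12 |
| 16 v 16 | 2.02% | 4.14% | 12 |
| 15 v 15 | 1.77% | 4.33% | 20 |
| 17 v 16 | 3.52% | 4.03% | 4 |
| 17 v 15 | 3.40% | 4.70% | 6 |
| 16 v 15 | 2.97% | 4.76% | 8 |

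In all six splits no table is rejected by Fisher and accepted by Boschloo. At 17 v 17 the additional tables include 8 v 2, 9 v 3 and 10 v 4 (Fisher p = 0.057, 0.071 and 0.080).

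**4. Power.** The same sum is used, with a different rate in each group. All rates are assumptions. One pair is built from the protocol's counts: 2.4 visits per year, and 2.4 − 1.0 = 1.4, over the 24-week intervention. If counts are Poisson, 1 − exp(−2.4 × 24/52) = 67% and 1 − exp(−1.4 × 24/52) = 48%. The other pairs are illustrations. Entries are Fisher → Boschloo in per cent, with the higher-rate group listed first.

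| Rates | 17 v 17 | 15 v 15 | 17 v 16 | 17 v 15 | 16 v 15 |
|---|---|---|---|---|---|
| 67% v 48% | 12.9 → 18.4 | 9.0 → 16.8 | 16.5 → 17.1 | 14.0 → 18.5 | 14.1 → 17.6 |
| 50% v 20% | 31.9 → 43.1 | 24.6 → 37.3 | 34.8 → 38.7 | 37.2 → 41.6 | 31.0 → 39.9 |
| 60% v 20% | 56.1 → 66.3 | 44.7 → 59.9 | 59.3 → 61.5 | 60.7 → 63.5 | 53.8 → 61.9 |
| 30% v 10% | 18.6 → 20.9 | 14.9 → 25.6 | 20.1 → 21.8 | 21.6 → 23.3 | 18.1 → 19.7 |

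The gain runs from about 2 to 15 points with equal groups and from about 1 to 9 with unequal ones. Some pairs fall slightly outside. 70% v 30% gains 15.6 points at 15 v 15 but only 0.3 at 17 v 16. When events are rare the gain can vanish: 20% v 5% at 17 v 17 moves from 11.6% to 11.7%.

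**5. Several tests together.** Take two proportions at two looks, treated for illustration as independent and each at its maximum size for 17 v 17. The chance of at least one false positive is 1 − (1 − 0.0244)⁴ = 9.4% with Fisher and 1 − (1 − 0.0431)⁴ = 16.2% with Boschloo.

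**The case against.** The strongest reply is that nothing here is wrong. Fisher's test is a standard choice for small two-group proportions, 5% is a ceiling, and the test respects it. Whether to condition on the margins is a matter of method on which statisticians differ. This stands, and it limits the point to efficiency.

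A reader might infer that the true error can never exceed 2.4%, or that it always stays under half of 5%. The protocol does not support that. It expects dropout and does not assure equal analysed groups, and the loss of a single patient (17 v 16) raises Fisher's maximum to 3.5% and shrinks the gain.

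A reader might also infer that the switch is free. It needs no more patients and keeps each test at or below 5%. But section 10.2 repeats the tests at 12 weeks, there are several primary endpoints, and the protocol states no adjustment. Fisher's slack then acts as an incidental buffer, as step 5 of the working shows. That part of the objection stands as a condition on the fix. It does not make Fisher's conservatism a form of multiplicity control, because the slack depends on how the dropouts happen to fall.

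Finally, the only rates built from the protocol's figures give under 20% power with either test. The change does not rescue this comparison.

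**Conclusion.** The point holds as a minor efficiency improvement. At the planned 17 v 17, Fisher's test uses at most 2.4% of the permitted 5%; across the splits examined its maximum lies between 1.8% and 3.5%. In each of them Boschloo's test keeps the 5% ceiling, never has lower power, and usually has more.

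The maximum sizes rest only on two independent binomial samples. The power gains also rest on assumed event rates, and they depend on the final split.

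It would be tempting to read the lost power as a departure from the stated 80%. The documents do not support that: the 80% belongs to a difference in mean visit counts (section 9.2), and no power is claimed for the proportions.

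**What to change.** In section 10.1, replace Fisher's exact test with Boschloo's exact unconditional test, two-sided at 5%, for the proportions of patients with a temporary visit and with a readmission. Report the risk difference with an exact unconditional confidence interval. Make the change before any outcome data are seen.

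State that the test is run at the level allotted to each primary endpoint and to the 12-week look. If that level is below 5%, the rejection region must be recalculated for it.

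The cost is about two sentences of text and possibly software other than the named SPSS version 21.0. The trade-off is that more of each nominal level is used, so switching without dividing the error rate would raise the overall chance of a false positive.

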# Overview

- 1. **Schema**

|  | Patients with chronic respiratory failure receiving NPPV during outpatient visits | | | | | | | |  |
| --- | --- | --- | --- | --- | --- | --- | --- | --- | --- |
|  |  |  |  |  |  |  |  |  |  |
|  | During a routine outpatient visit, the attending physician or physician in charge will provide an overview of the study, to seek for patients who are willing to participate in the research | | | | | | | |  |
|  |  |  |  |  |  |  |  |  |  |
|  |  | Researcher explains the research overview, consenting participants fills out the consent form and are registered | | | | | |  |  |
|  |  |  |  |  |  |  |  |  |  |
|  | At enrollment (baseline)  Primary endpoint: Number of hospitalizations, number of hospital days, and number of unscheduled outpatient visits in the past 3 months  Secondary endpoints: SGRQ score, EQ-5D index, SCAQ responses, respiratory function test, and 6-min walk test | | | | | | | |  |
|  |  |  |  |  |  |  |  |  |  |
|  |  |  |  |  |  |  |  |  |  |
|  |  |  |  |  |  |  |  |  |  |
|  |  | Allocation (allocation adjustment factor: facility) | | | | | |  |  |
|  |  |  |  |  |  |  |  |  |  |
|  |  |  |  |  |  |  |  |  |  |
| Intervention group:  Usual outpatient care + tele-nursing intervention program | | | | |  | Control group:  Usual outpatient care | | | |
|  |  |  |  |  |  |  |  |  |  |
|  |  |  |  |  |  |  |  |  |  |
| Regular outpatient care (once/month)   1. Medical treatment by a physician 2. Health consultation and information by nurses   Remote nursing intervention program (1 time/day, 3 months)  Remote monitoring  Once a day  Observation of information input to the tablet  Input items: Vital signs, respiratory symptoms, food intake, excretion, medication, and physical symptoms other than respiratory symptoms  2. Health counseling and information provision  Health consultation and information provision via videophone once a day for approximately 30 min when triggers are applicable or when the participant wishes | | | | |  | Regular outpatient care (once/month)   1. Medical treatment by a physician 2. Health consultation and information by nurses | | | |
|  |  |  |  |  |  |  |  |  |  |
|  |  |  |  |  |  |  |  |  |  |
|  |  |  |  |  |  |  |  |  |  |
|  |  |  |  |  |  |  |  |  |  |
|  |  |  |  |  |  |  |  |  |  |
|  |  |  |  |  |  |  |  |  |  |
|  |  |  |  |  |  |  |  |  |  |
|  |  |  |  |  |  |  |  |  |  |
|  |  |  |  |  |  |  |  |  |  |
|  |  |  |  |  |  |  |  |  |  |
|  |  |  |  |  |  |  |  |  |  |

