
The web-based program in the tele-nursing system consists of a patient site and a researcher site. The tablet terminal at the patient site has (1) a screen for recording daily physical condition, (2) a screen for video calls, (3) a screen for SNS input, and (4) a screen for respiratory rehabilitation information. The researcher's site will have (1) a list of the participant's telemonitoring data and (2) a screen for inputting comments. The researcher can check the participant's daily records and output the changes over time on a summary sheet.

The intervention period will be 24 weeks, and the number of ad hoc visits and readmissions during the past 12 and 24 weeks (primary endpoints) will be examined by the researcher at enrollment, 12 weeks after enrollment, and 24 weeks after enrollment, using the electronic medical record. At enrollment and at regular outpatient visits 12 and 24 weeks after enrollment, researchers will conduct a questionnaire survey about daily life, and perform respiratory function and 6-minute walk tests. In addition, activity meters will be checked 12 and 24 weeks after enrollment to collect data on the average number of steps and patient activity. Respiratory function and 6-min walk tests at enrollment as well as 12 and 24 weeks after enrollment will be performed by the researcher using equipment purchased using the research fund, since these tests are not covered by insurance and are outside the scope of usual medical care. Since the primary endpoints of this study are the number of emergency visits and rehospitalizations due to acute exacerbations of chronic respiratory diseases, the intervention will not be stopped in the event of worsening symptoms due to acute exacerbations. If the participant dies, the intervention is terminated because the study cannot continue. If a participant requests that the intervention be continued after their participation in the program, the intervention may be offered for an extended period of time, regardless of whether the participant is in the intervention or control group.

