# Survey Schedule

|  | **Evaluation item** | **Survey schedule** | | |
| --- | --- | --- | --- | --- |
|  |  | **At enrollment**  **(Baseline)** | **12 weeks after enrollment** | **24 weeks after enrollment** |
| **Interview or medical record** | Basic patient information | ◯ |  |  |
|  | Occasional visits and readmissions in the past 12 weeks | ◯ | ◯ |  |
|  | Occasional doctor visits and readmissions in the past 24 weeks | ◯ |  | ○ |
| **Questionnaire** | SGRQ | ◯ | ◯ | ◯ |
|  | EQ-5D | ◯ | ◯ | ◯ |
|  | SCAQ | ◯ | ◯ | ◯ |
| **Objective assessment items** | Respiratory function test | ◯ | ◯ | ◯ |
|  | 6-min walk test | ◯ | ◯ | ◯ |
|  | Average number of steps, activity level |  | ◯ | ◯ |

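### The unadjusted t-test on visit and readmission counts is valid but leaves unused the baseline counts and the allocation facility, which the trial already records

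*Protocol*

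**What the plan says.** Statistical analysis methods fixes the comparison of the two primary counts: "student *t*-test will be used to compare the number of temporary visits and readmissions between groups", two-sided at 5%. No covariate, facility term or observation time is mentioned. The section on interim analysis applies the same methods at 12 weeks.

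Other sections show what is available to the analysis:

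- The Survey Schedule lists "Occasional doctor visits and readmissions in the past 24 weeks" as an item collected at enrolment and again at 24 weeks. A matching 12-week item is collected at enrolment and at 12 weeks.
- The schema in the Overview reads "Allocation (allocation adjustment factor: facility". The Allocation section gives the reason: facilities are expected to differ in their medical systems.
- Basis for setting says: "The significance level, power of the study, and standard deviation of the number of improvement of visits are 5%, 80%, and 1.0 visit/year, respectively". An SD of improvement reads most naturally as the SD of a change from baseline, whereas the planned test compares the follow-up counts themselves.

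**The concern.** Past exacerbation visits are the most direct measure in this protocol of how often a patient is likely to attend. With 17 patients per group, chance differences in that underlying rate can be a large part of the error in the comparison. Adjusting for the baseline count removes some of it at no cost in data collection. Facility is treated as important enough to structure the allocation and is then left out of the analysis.

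This method is written into the protocol, not left open for a later plan. What is at stake is efficiency: a wider confidence interval than the collected data would support, in a trial with few patients. The validity of the p-value is not in question.

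**Working it through.** **The plan's own figure.** Inputs from Basis for setting: difference 1.0 visit/year, SD 1.0 visit/year, two-sided 5%, power 80%, dropout 10%.

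n per group = 2 × (1.960 + 0.842)² × 1.0² / 1.0² = 15.70, so 16. Allowing for dropout, 15.70 / 0.9 = 17.4. This is 17 to the nearest integer and 18 rounded up, so the stated 17 is reproduced to within rounding.

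**Expected 24-week counts.** The protocol gives "2.4 visits/year for NPPV users and 1.6 visits/year for NPPV non-users" and assumes a reduction of 1.0 visit/year.

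- Control: 2.4 × 24/52 = 1.11
- Intervention: 1.4 × 24/52 = 0.65
- Difference: 0.46

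**What baseline adjustment buys.** Let the variance of a count be μ + kμ², where k is the between-patient dispersion. The protocol does not give k, so I take 0 to 2. If baseline and follow-up share the same patient-level rate with mean μ = 1.108, their correlation is ρ = kμ / (1 + kμ). Estimating one slope from 34 patients costs a factor of about 1 + 1/(34 − 4) = 1.033. The variance of the adjusted difference relative to the unadjusted one is therefore about (1 − ρ²) × 1.033.

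| k (assumed) | ρ | 1 − ρ² | × 1.033 | Simulated ratios |
|---|---|---|---|---|
| 0 | 0 | 1.00 | 1.03 | 1.03 |
| 0.5 | 0.36 | 0.87 | 0.90 | 0.91 |
| 1 | 0.53 | 0.72 | 0.75 | 0.73 to 0.76 |
| 2 | 0.69 | 0.53 | 0.54 | 0.53 to 0.58 |

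The simulations used 17 per group, a gamma-distributed patient rate shared by both periods, control mean 1.108 and rate ratio 1.4/2.4. The formula uses the control mean in both groups. The two agree closely. Both refer to linear adjustment for the baseline count alone.

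**Power on 24-week counts.** t-test against quasi-Poisson adjusted for baseline only:

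- k = 0.5: 21.4% and 22.7%
- k = 1: 15.3% and 18.6% (a separate run gave 17% and 20%)
- k = 2: 9.6% and 17.1%

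Type I error of the adjusted analysis was 4-6%.

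**Adding facility.** The number of facilities is not available here, so it is an assumption. Power of the t-test against quasi-Poisson with baseline and facility terms:

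| k | Three facilities that differ (rates 0.8, 1, 1.2) | Five facilities that do not differ |
|---|---|---|
| 0 | 26.0% and 23.4% | 27.9% and 22.1% |
| 0.5 | 19.4% and 19.4% | 19.8% and 18.1% |
| 1 | 15.3% and 17.3% | 16.8% and 17.6% |

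In the three-facility runs, linear adjustment for baseline and facility changed the mean standard error from 0.319 to 0.321 at k near 0, from 0.380 to 0.363 at k = 0.5 and from 0.436 to 0.375 at k = 1.

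**The case against.** The strongest reply is that this is a preference. Randomisation makes the t-test valid, and leaving out an allocation factor usually makes it slightly conservative. The gain depends on a dispersion the protocol does not give. It becomes a small loss if patients do not differ in rate, and it is a best case because one rate is assumed to drive both periods perfectly. Primary data come chiefly from patients' own reports, so recall error would weaken the correlation. Facility terms can use up the gain, as the table shows. A rate ratio also departs from the mean difference behind the sample size. All of this stands. It limits the size of the point, but it gives no reason to set aside a baseline count that is already collected.

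A reader might go further and infer that raw counts reward early death or withdrawal. The protocol does say "If the participant dies, the intervention is terminated because the study cannot continue", and it assumes 10% dropout. It does not say whether an early leaver's partial count enters the test or the patient is excluded, so bias in the plan as written cannot be asserted. If partial counts were used and 10% of each group left at half time, the expected difference would shrink from 0.46 to 0.46 × 0.95 = 0.44. A false benefit needs unequal exit between groups.

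A reader might also infer bias from late enrolment. On the registration and research periods in the Overview, taking month-ends, 31 October 2018 to 31 March 2019 is 151 days, or 21.6 weeks. The shortfall is at most 2.4 weeks, and it does not depend on group.

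**Conclusion.** The point holds as a loss of precision. The protocol fixes an unadjusted test while collecting a strong candidate covariate and allocating by facility. Baseline adjustment changes the variance of the group difference by about +3% at dispersion 0, -9% at 0.5, -25% at 1 and -45% at 2, assuming baseline and follow-up counts share a patient-level rate. At dispersion 1 power rises from about 15-17% to 19-20%, so adjustment does not solve the shortage of power. The documents do not support a claim that the planned test is invalid, or that it is biased by death, withdrawal or late enrolment. The change is worth making because it costs only wording, and its benefit should be described as modest and dependent on assumptions.

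**What to change.** For visits and for readmissions separately, make the primary comparison of the 24-week count one pre-specified model, for example quasi-Poisson. Its terms are group, log(baseline 24-week count + 0.5) and facility, with small facilities pooled by a rule set in advance. Use log(weeks observed) as offset, so that any partial follow-up is not read as fewer events. Report the rate ratio with its 95% CI, and keep the t-test as a sensitivity analysis. If the interim analysis is to use the same method, its covariate is the baseline 12-week count.

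No new data are needed. The costs are:

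- The effect measure becomes a rate ratio, while the sample size rests on a mean difference.
- Facility terms use a few degrees of freedom and can cancel the gain if facilities do not in fact differ.
- There is a slight loss if patients do not differ in underlying rate.
- The offset does not remove bias from deaths related to exacerbation, because observation time is then linked to the visit rate.
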